# **7.** **Endpoint**

## **7-1.** **Items related to the evaluation of efficacy**

　Primary outcomes

1) Incidence rate of intraoperative thrombotic complications

It is defined as the proportion of patients with evidence of cerebral angiographically evident thrombus formation in the vicinity of the aneurysm neck or parent artery during surgery.

2) Incidence rate of symptomatic ischemic lesions on MRI diffusion-weighted imaging (DWI) evaluated by the Independent Review Committee (IRC)

It is defined as the percentage of patients with acute-phase ischemic lesions on MRI-DWI performed 6–48 h postoperatively and with concordant neurologic findings.

Key secondary outcomes

1) Incidence rate of all bleeding events within 14 days of enrollment

As a basic protocol, a head CT is performed within 48 h postoperatively and at 14±2 days postoperatively. Additionally, imaging evaluations were conducted as required. The incidence rate of all bleeding events is defined as the percentage of patients with a ruptured aneurysm (symptomatic subarachnoid or intracerebral hemorrhage due to rupture of an aneurysm of interest), a hemorrhagic stroke (symptomatic subarachnoid and intracerebral hemorrhage not due to rupture of target aneurysm, or the proportion of patients who experienced "major hemorrhage" according to ISTH criteria within 14 days post-registration.

2) Incidence rate of cerebral ischemic events in the first 14 days after MRI

The basic protocol is head CT performed within 6–48 h after surgery and 14 ± 2 days after surgery. This is defined as the percentage of patients with transient ischemic attack within 14 ± 2 days after MRI (neurological symptoms lasting less than 24 h with or without imaging findings) or ischemic stroke (focal neurological symptoms lasting more than 24 h and ischemic lesions confirmed by head CT or MRI) during the study period.

Other secondary outcomes

1) Incidence rate of symptomatic ischemic lesions in MRI-DWI evaluated by INV.

2) mRS at 3 months

Assessment is based on mRS scoring 3 months after the onset of subarachnoid hemorrhage.

　Exploratory outcomes

1) Ischemic lesions on MRI-DWI (number and size: 0–4 mm, 5–9 mm, 10–14 mm, 15 mm or greater, categorized as IRC or INV)

2) Incidence rate of cerebral hemorrhage along the tube tract for ventricular drainage on CT scans in the first 14 days after EVT.

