|  | Number of ischemic lesions other than the area of the aneurysm's parent artery | | | | | 0 – 4 mm |  |
|  |  | | | | | 5 – 9 mm |  |
|  |  | | | | | 10 – 14 mm |  |
|  |  | | | | | 15 mm or higher |  |
| MRA | Degree of aneurysm embolization | | | | | CO, NR, BF | |
|  | Newly occluded vessels | | | | | Yes, no | |
| CT examination (within 48 h after surgery) | | | | | | | |
| Date and time of survey | | | (yyyy/mm/dd/HH/mm) | | | | |
| Increased subarachnoid hemorrhage | | Yes, no | | | | | |
|  | | Modified Fisher grade | | | 0, 1, 2, 3, 4 | | |
| Increase in cerebral parenchymal blood species | | Yes, no | | | | | |
|  | | Size (maximum diameter) | | | | | |
| New parenchymal brain hematoma | | Yes (maximum diameter), no | | | | | |
| Increased hydrocephalus | | Yes, no | | | | | |
| Appearance of cerebral hemorrhage along tube tract  (only for cases with ventricular drainage) | | | | Yes (maximum diameter), no | | | |
| Surgical procedure after cerebral aneurysm treatment (during period after surgery to MRI scan), (multiple responses possible) | | | | | | | |
| Yes (ventricular drainage, spinal drainage, decompressive craniectomy, hematoma evacuation, cerebral aneurysm neck clipping, other), no | | | | | | | |
| Date of enforcement | | | | (yyyy/mm/dd) | | | |
| Antithrombotic therapy (during the period after surgery to MRI scan) | | | | | | | |
| Yes (detail), no | | | | | | | |
| Worsening of neurologic manifestations (during the period after surgery to MRI scan) | | | | | | | |
| Yes (disturbed consciousness, paralysis, sensory disturbance, aphasia, hemispatial neglect, others [details]), no | | | | | | | |

Observation period (14 days after surgery), acceptable range: ±2 days

| Day of investigation |
| --- |

| Day of investigation | (yyyy/mm/dd) |
| --- | --- |

| Subject information |
| --- |

| Continuous intravenous Nicardipine Hydrochloride therapy | Yes, no |
| --- | --- |
| IV Fasudil Hydrochloride Hydrate therapy | Yes, no |
| IV Ozagrel Sodium therapy | Yes, no |
| New cerebral infarction due to cerebral vasospasm | Yes, no |
| Endovascular treatment for symptomatic cerebral vasospasm. | Yes, no |
|  | Procedural details (), date, and time (). |

| Other antithrombotic therapies present |
| --- |
| Yes (detail), no |
| Safety information |

| Serious adverse event | Yes (if "yes", report details of "event/adverse event/occurrence of re-treatment"), no |
| --- | --- |

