| Retreatment | Yes (if "yes", report details of "event/adverse event/occurrence of re-treatment"), no |

| CT |
| --- |

| Date and time of survey | (yyyy/mm/dd) |
| --- | --- |

| Increased subarachnoid hemorrhage | Yes, no | | |
| --- | --- | --- | --- |
|  | Modified Fisher grade | | 0, 1, 2, 3, 4 |
| Increase in cerebral parenchymal blood species | Yes (maximum diameter), no | | |
| New parenchymal brain hematoma | Yes (maximum diameter), no | | |
| Increased hydrocephalus | Yes, no | | |
| Appearance of cerebral hemorrhage along tube tract (only for cases with ventricular drainage) | | Yes (maximum diameter), no | |
| Surgical procedures after cerebral aneurysm treatment (multiple responses possible) | | | |
| Yes (ventricular drainage, spinal drainage, decompressive craniectomy, hematoma evacuation, cerebral aneurysm neck clipping, other), no | | | |

| Date of enforcement | (yyyy/mm/dd) |
| --- | --- |

| Worsening neurologic findings |
| --- |

| Yes (disturbed consciousness, paralysis, sensory disturbance, aphasia, hemispatial neglect, others (details)), no |
| --- |

Observation period (3 months after surgery) Acceptable range: ±14 days

| Day of investigation | |
| --- | --- |
| Day of investigation | (yyyy/mm/dd) |
| Subject information | |
| mRS | 0, 1, 2, 3, 4, 5, 6 |
| Shunt surgery for secondary hydrocephalus | Yes, no |
|  | Date (yyyy/mm/dd) |
|  | Ventriculoperitoneal shunt; lumbar peritoneal shunt; other |
| Safety information | |
| Serious adverse event | Yes (if "yes", report details of "event/adverse event/occurrence of re-treatment"), no |
| Retreatment | Yes (if "yes", report details of "event/adverse event/occurrence of re-treatment"), no |

Events, adverse events, and re-treatment occurrences (multiple responses possible)

| Event, adverse event, or retreatment | | |
| --- | --- | --- |
| Date of incident | (yyyy/mm/dd) | |
| Stroke events | | |
| Ruptured cerebral artery aneurysm | Treated aneurysm, otherwise (detail) | |
|  | WFNS Grade (I, II, III, IV, V) | |
|  | Retreatment: yes or no | |
|  | Date of retreatment | (yyyy/mm/dd) |
|  | Retreatment method | Craniotomy, endovascular treatment |
|  | Treatment outcome | CO, NR, BF |
| Other hemorrhagic stroke | Yes, no | |
|  | Details () | |
| Ischemic stroke | Yes, no | |
|  | Details () | |
| Other bleeding events | | |
| Significant hemorrhage by ISTH criteria  (Intracranial hemorrhage is described in the stroke event.) | Yes, no  Details () | |

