| 4 | Moderately severe disability; unable to walk without assistance and unable to attend to own bodily needs without assistance |
| 5 | Severe disability; bedridden, incontinent and requiring constant nursing care and attention |
| 6 | Dead |

Medical history and lifestyle habits.

|  | Definitions |
| --- | --- |
| Subarachnoid hemorrhage | Subarachnoid hemorrhage due to ruptured cerebral aneurysm not targeted in this study |
| Hemorrhagic stroke | Focal neurologic symptoms and confirmed intracranial hemorrhage by head CT or MRI |
| Ischemic stroke | Focal neurologic symptoms and confirmed cerebral infarction by head CT or MRI |
| High blood pressure | Any of the following criteria met within the three months prior to treatment: systolic blood pressure of 140 mmHg or higher, diastolic blood pressure of 90 mmHg or higher, or the use of antihypertensive medication to lower blood pressure. |
| Diabetes mellitus | Any of the following criteria met within the three months before treatment: fasting blood glucose of 126 mg/dL or higher, random blood glucose of 200 mg/dL or higher, HbA1c of 6.5% or higher, use of hypoglycemic agents, or a previous diagnosis of diabetes by a medical institution. |
| Dyslipidemia | Any of the following criteria met: LDL cholesterol of 140 mg/dL or higher, HDL cholesterol less than 40 mg/dL, triglycerides of 150 mg/dL or higher, or the use of lipid-lowering agents. |
| Smoking habit | Those who have a smoking habit of one or more cigarettes per day on average within 1 year before treatment. |

・Stroke events

　The following events occurring between surgery and 14 ± 2 days after surgery are defined as stroke events in this study:

|  | Definitions |
| --- | --- |
| Postoperative rupture of cerebral aneurysm | Symptomatic subarachnoid or intracerebral hemorrhage due to rupture　cerebral aneurysm after surgery diagnosed by CT or MRI. When asymptomatic or minimal headache occurs, the decision should be made with caution. WFNS Grade, presence or absence of retreatment, and treatment modalities should also be recorded. |
| Transient ischemic attack | Transient episodes of neurological dysfunction resulting from focal cerebral or retinal ischemia without evidence of acute infarction. Episodes of neurologic dysfunction should resolve within at least 24 h. |
| Ischemic stroke | Those with focal neurological symptoms lasting more than 24 h and confirmed ischemic by head CT or MRI. |

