| Hemorrhagic stroke | Symptomatic subarachnoid and intracerebral hemorrhage without rupture of target cerebral aneurysms after surgery diagnosed by CT or MRI. This is not the case if the symptom is only a headache and not accompanied by other objective neurological symptoms. |

The above transient ischemic attack and ischemic stroke are combined to define a global ischemic event.

・Bleeding events

The following events that fall under "major bleeding" according to ISTH criteria are included in the "bleeding events" of this study.

1. Fatal bleeding

2. Symptomatic hemorrhage (intracranial, intrathecal, intraocular, retroperitoneal, intraarticular or intrapericardial, or intramuscular hemorrhage with muscular compartment syndrome) at critical sites or organs.

3. Bleeding resulting in a decrease in Hb level of 20 g/L or higher, bleeding leading to whole blood transfusion, or transfusion of two or more units of red blood cells.

・Cause of death

| Cerebral aneurysm death | Death from rupture of a cerebral aneurysm or from events directly related to a cerebral aneurysm |
| --- | --- |
| Death from stroke | Death from ischemic stroke and hemorrhagic stroke due to causes other than cerebral aneurysm |
| Other deaths | Death from causes other than cerebral aneurysm and stroke |
| Unknown | Death from unknown causes |

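### Key secondary 2 (TIA or ischemic stroke after the MRI) is not captured reliably: TIA has no item, vasospasm infarcts have no date or entry rule, and its two definitions conflict

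*Protocol*

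**What the plan says.** **Endpoint, Protocol section 7-1, key secondary outcome 2.** The TIA part reads: "This is defined as the percentage of patients with transient ischemic attack within 14 ± 2 days after MRI", with TIA described as "neurological symptoms lasting less than 24 h with or without imaging findings". The other part is "ischemic stroke (focal neurological symptoms lasting more than 24 h and ischemic lesions confirmed by head CT or MRI) during the study period". No cause is named or excluded.

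**Event definitions, Protocol section 8.** The lead-in is "The following events occurring between surgery and 14 ± 2 days after surgery are defined as stroke events in this study". Four events follow: postoperative aneurysm rupture, TIA, ischemic stroke and hemorrhagic stroke. TIA is here "Transient episodes of neurological dysfunction resulting from focal cerebral or retinal ischemia without evidence of acute infarction". The two ischemic events are then joined: "The above transient ischemic attack and ischemic stroke are combined to define a global ischemic event".

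**Data items, Protocol section 8.** The stroke part of the event form covers aneurysm rupture, other hemorrhagic stroke and "Ischemic stroke | Yes, no", under a calendar date of incident. The day-14 form has the item "New cerebral infarction due to cerebral vasospasm", answered yes or no.

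**Analysis, Protocol section 14-3.** Both key secondary endpoints are judged by the upper 95% confidence limit of the aspirin-minus-placebo difference. Non-inferiority is declared if that limit is below 10%.

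**The concern.** A composite endpoint needs a place to record each component and one rule for which events belong to it. Here one of the two components has no item of its own. A second source of qualifying events, symptomatic vasospasm infarcts, is collected in a form that shows neither when the event happened nor whether it met the symptom-duration criterion. The text that defines the endpoint exists in two versions that would classify some patients differently.

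This matters because of the direction of the test. In a superiority comparison, missed events mostly cost power. In a non-inferiority comparison on a risk difference with a fixed margin, they pull the difference toward zero and narrow the interval, and both make it easier to pass. A statistical analysis plan can choose between definitions, but it cannot recover a TIA that nobody recorded.

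**Working it through.** **1. Defined events against listed items (section 8)**

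| Defined stroke event | Item on the event form |
| --- | --- |
| Postoperative aneurysm rupture | yes |
| Hemorrhagic stroke | yes |
| Ischemic stroke | yes, with details and date |
| TIA | none |

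TIA is the only one without an item. The remaining routes are weak:
- The day-14 form points to the event form only through its serious-adverse-event and retreatment questions, and a TIA need not be either.
- The adverse events that section 7-2 names for recording are death, major hemorrhage, retreatment and rebleeding.
- What is left is the schedule's general event row and the free-text line for other adverse events.

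**2. The vasospasm item against the ischemic stroke definition**

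To count, an ischemic stroke needs focal symptoms beyond 24 h, a lesion on CT or MRI, and an onset inside the window. A yes to the vasospasm item asserts an infarct and a cause. It gives no onset date, symptoms or duration. The row for endovascular treatment of vasospasm on the same form does carry a date and time. No text says that a yes also requires an event form.

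**3. The two windows**

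The MRI is 6 to 48 h after surgery, that is 0.25 to 2 days.
- Section 7-1, counted from the MRI: the window ends 14 ± 2 days later, so between 0.25 + 12 = 12.25 and 2 + 16 = 18 days after surgery.
- Section 8, counted from surgery: the window ends at 12 to 16 days.

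An ischemic stroke between surgery and the MRI is inside the section 8 window and outside the section 7-1 window. That is the interval which primary outcome 2 already covers.

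**4. The two TIA definitions**

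Take a patient with symptoms for less than 24 h and an acute infarct on imaging. Under section 7-1 this is a TIA and counts. Under section 8 it is not a TIA, because infarction is present, and not an ischemic stroke, because symptoms did not exceed 24 h. The patient counts under one text and not under the other.

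**5. What missed events do to the test**

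The protocol states no event rate or power for this endpoint. Its 230 per arm (section 14-2) was set for the primaries: 15% against 5%, two-sided 2.5%, 90% power. That figure reproduces: exact power of Fisher's test at 230 per arm is 90.2%. I use 230 per arm below.

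Assumptions: placebo rate p of 10%, 20% or 30%; true aspirin rate p + 10 points, exactly at the margin; a fraction c of events captured, the same in both arms.

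- Observed difference: 0.10 × c
- SE = √{[c(p+0.10)(1 − c(p+0.10)) + cp(1 − cp)] / 230}
- Probability of declaring non-inferiority = Φ[(0.10 − 0.10c)/SE − 1.96]

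Example, p = 20%, c = 0.80: observed 24% against 16%, difference 8 points. SE = √[(0.24 × 0.76 + 0.16 × 0.84)/230] = 0.0371. Then 0.02/0.0371 − 1.96 = −1.42, and Φ = 7.8%.

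| Captured | p = 10% | p = 20% | p = 30% |
| --- | --- | --- | --- |
| 100% | 2.5% | 2.5% | 2.5% |
| 90% | 5.0% | 4.4% | 4.2% |
| 80% | 9.8% | 7.8% | 6.9% |
| 70% | 18.3% | 13.4% | 11.3% |

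With no true difference and full capture, the same formula gives a chance of passing of 95% at a 10% event rate, 85% at 15% and 77% at 20%. Whether vasospasm infarcts are counted can therefore change how demanding the test is.

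**The case against.** The strongest reply is that the data are mostly there. Ischemic stroke has its own dated item with details, and the MRI has a date and time. TIA is a defined event, section 6 says that all cerebral ischemic events will be evaluated, and the day-14 form asks about neurological worsening by type. Section 8 lists items, and the electronic form itself is not shown. This stands to a degree. A reader might infer that the endpoint cannot be built at all, and the documents do not support that: the ischemic stroke part can be built, and a TIA can be written as free text. What fails is reliable capture. The worsening item has no date or duration and does not identify a TIA.

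A reader might also infer that pooling vasospasm infarcts with thromboembolic events is an error, given a single preoperative dose. It is not. All-cause ischemia is the stated scope in section 6, and neither definition excludes a cause. Procedural thromboembolism is already addressed by the two primaries. A claim that pooling widens the interval by some multiple would rest on an invented vasospasm rate, and a wider interval makes non-inferiority harder to declare, not easier.

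On timing, an event on the day of the MRI has only a calendar date. However, the early postoperative form separately records worsening between surgery and MRI, which helps order such events. The remaining ambiguity is small.

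**Conclusion.** The point holds as a defect of capture and definition. Three facts rest on the text alone: TIA is the only defined stroke event without an item; the vasospasm-infarct item has no date, symptoms, duration or entry rule; and sections 7-1 and 8 conflict on the window and on TIA.

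The size is conditional. If 10% to 30% of events go unrecorded equally in both arms, the false non-inferiority rate at a true 10-point excess rises from 2.5% to between about 4% and 18%, over assumed placebo rates of 10% to 30%. Neither the capture fraction nor the event rate is in the protocol, and unequal capture between arms would behave differently. The primary endpoints are not affected. This should be changed, because the loss occurs at data entry.

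**What to change.** - Add a TIA item to the event form, with date and time, and add an onset time to the ischemic stroke item.
- Instruct sites to enter every symptomatic infarct attributed to vasospasm on the event form as well, with onset date, symptom duration and cause.
- Reconcile sections 7-1 and 8: one start point, one end point that applies to both components, and one TIA definition. State explicitly that vasospasm infarcts meeting the ischemic stroke definition count.
- Keep all-cause ischemia as the key secondary outcome. A descriptive table by cause is optional.

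The cost is a few form fields, one entry instruction and a wording amendment. Cause remains an investigator judgment, which the day-14 form already requests. If patients are already enrolled, sites would need to be asked about past TIAs and about the onset and symptoms behind each vasospasm item answered yes, while allocation is still blinded.

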# **9.** **Discontinuation criteria**

- When it is judged impossible to continue the study for any reason, the physician-in-charge should discontinue the administration of the study drug and specify the date and timing of discontinuation or dropout, the reason for discontinuation or dropout, and course in the medical records and eCRF, as well as conduct necessary examinations at the time of discontinuation or dropout to evaluate efficacy and safety.

## 9-1. Discontinuation within the time from post-registration allocation to embolization

Discontinuation criteria

　　 1) When the research subject was asked to decline participation or withdraw consent

　　　2) When it is found that the eligibility criteria are not met after registration

　　 3) When the general condition deteriorates due to the re-rupture of the cerebral aneurysm, the surgery is discontinued.

4) When the entire study is discontinued

5) When the physician considers it appropriate to discontinue the study for other reasons

## 9-2. Discontinuation during the period from embolization to 3 months after surgery

Discontinuation criteria

1) When a participant has offered to decline research participation or withdrawn consent

2) When it is found that the eligibility is not satisfied after registration

3) When the entire study is discontinued

4) When the physician considers it appropriate to discontinue the study for other reasons

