## **6-3.** **Dosage and administration and duration of administration of the research drug**

After obtaining and assigning informed consent, when performing aneurysm embolization for a ruptured cerebral aneurysm, a nasogastric tube is inserted after induction of general anesthesia, and aspirin-powder 200mg or placebo-lactose 200mg is dissolved in tepid-water 20mL via a nasogastric tube.

・Aspirin (Aspirin)

Date of approval: August 6, 1985

　Approval Number: 16000AMZ03805000

　Manufactured and marketed by Mylan Pharmaceutical Co., Ltd.

　Sales: Pfizer Pharmaceuticals Inc.

　Dosage form: powder (crystals)

　Storage: Storage at room temperature

・Lactose (Lactose Hydrate)

Manufacturing approval Date: February 1, 2008

Approval Number: 27A2X00206

Manufactured and marketed by Mylan Pharmaceutical Co., Ltd.

　Sales: Pfizer Pharmaceuticals Inc.

Dosage form: powder (crystals)

　Storage: Storage at room temperature

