## **14-1. Full analysis set**

　　The definitions of the analyzed population are as follows:

　Intention-to-treat (ITT) Group

All randomized populations will be included.

・Modified intention-to-treat (mITT) group

Patients in the ITT population excluded: ① patients who had never received a treatment either aspirin or placebo; ② patients who did not have any post-randomization data; and ③ patients who met the well-defined and objectively determinable criteria for selection and exclusion.

・Safety analysis set (Safety Analysis Set; SAS)

The study population will be randomized and will receive the treatment (aspirin or placebo).

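### Section 9-2 allows discontinuation of already-dosed patients for late-found ineligibility or at the physician's discretion, and nowhere says that outcome follow-up continues

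*Protocol*

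**What the plan says.** Section 6-3 describes one administration before embolization: "a nasogastric tube is inserted after induction of general anesthesia, and aspirin-powder 200mg or placebo-lactose 200mg is dissolved in tepid-water 20mL via a nasogastric tube". No further dose of study drug is planned.

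Section 9-2 is titled "Discontinuation during the period from embolization to 3 months after surgery", so it lies wholly after dosing. It lists four grounds:
- criterion 1: refusal or withdrawal of consent;
- criterion 2: "When it is found that the eligibility is not satisfied after registration";
- criterion 3: termination of the whole study;
- criterion 4: "When the physician considers it appropriate to discontinue the study for other reasons".

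The general rule in section 9 says that "the physician-in-charge should discontinue the administration of the study drug and specify the date and timing of discontinuation or dropout". It also tells the physician to record the reason and course, and to "conduct necessary examinations at the time of discontinuation or dropout to evaluate efficacy and safety".

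Section 14-1 defines three sets. For ITT, "All randomized populations will be included". The safety set is everyone randomized and dosed. The modified intention-to-treat (mITT) set has a third exclusion tied to the eligibility criteria. Its wording is unclear, but it appears meant to remove ineligible patients. Section 14-3 analyses the primary, key secondary and other secondary endpoints in mITT, and adverse events in the safety set.

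**The concern.** After embolization the instruction to stop study drug has nothing to act on. The only thing that can still be discontinued is observation. Section 9-2 itself speaks of discontinuing the study, and section 9 treats discontinuation and dropout alike. A site would reasonably read the two together as ending follow-up.

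Criteria 1 and 3 are proper reasons for that; criteria 2 and 4 are not. Criterion 4 has no limits and is applied by a physician who may already know how the patient has fared. That physician may also know the allocation if the emergency key was opened. Section 6 and section 6-4 allow this for intraoperative thrombus, which is itself the first primary outcome, for stent placement and for certain serious adverse events. Criterion 2 can also arise after dosing: an attempted parent artery occlusion or simultaneous treatment of a second aneurysm (exclusions 2 and 5) may become apparent only during the procedure.

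At stake is whether outcomes are missing for reasons related to outcome or treatment. An analysis plan can handle missing data, but it cannot restore observations that were never made.

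**Working it through.** **1. What a post-dose discontinuation can remove**

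| Outcome | When observed | Exposed? |
|---|---|---|
| Primary 1, intraoperative thrombus | during surgery | no, already observed |
| Primary 2, symptomatic DWI lesion | MRI at 6-48 h | yes, if discontinued before MRI |
| Bleeding events | 14 days from enrollment | yes |
| Ischemic events | 14 days after MRI | yes |
| mRS | 3 months | yes |

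The examination at discontinuation recovers the status on that day, but not the later assessments.

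**2. Which analyses are affected**
- Criterion 4: the patient was dosed and eligible and has post-randomization data, so no mITT exclusion applies. The loss falls on the mITT analyses, including both non-inferiority comparisons and mRS.
- Criterion 2: if the third mITT exclusion removes ineligible patients, they leave those analyses in any case. The loss falls on the safety set and on ITT, although section 14-3 assigns no analysis to ITT.

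**3. The plan's own allowance for loss**

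Section 14-2: 460 / (1 − 0.05) = 484.2, stated as 484. The allowance is 484 − 460 = 24 patients, 12 per arm, or 24/484 = 5.0%. It covers all causes and is not a rate for criteria 2 and 4.

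**4. Bias in the bleeding difference**

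The protocol gives no bleeding rate and no discontinuation rate, so these inputs are assumptions. Let a fraction d of the aspirin arm only be lost, with bleeding rate p_L among those lost and p_R = 10% among those retained.

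- True aspirin rate = (1 − d)·p_R + d·p_L
- Observed rate = p_R
- Understatement = d·(p_L − p_R)

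| d | p_L | Understatement |
|---|---|---|
| 5% | 30% | 0.05 × 0.20 = 1.0 point |
| 5% | 50% | 0.05 × 0.40 = 2.0 points |
| 10% | 30% | 0.10 × 0.20 = 2.0 points |
| 10% | 50% | 0.10 × 0.40 = 4.0 points |

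The margin in section 14-3 is 10 points on the upper 95% limit of aspirin minus placebo, so this error favours declaring non-inferiority. If the same pattern of loss occurred in both arms, it would largely cancel. If it occurred in the placebo arm only, it would act the other way.

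**5. Loss of power is the smaller issue**

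With equal true rates p, SE = √(2p(1 − p)/n) and power = Φ(0.10/SE − 1.96).
- p = 10%: 95.6% with 242 per arm, 94.7% after 5% loss, 93.6% after 10% loss.
- p = 20%: 78.5%, 76.4% and 74.2%.

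Uninformative loss costs a few points of power at most. The concern is informative loss.

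**The case against.** The strongest reply is that the protocol never says observation stops. Section 9 speaks of stopping drug, recording reasons and examining the patient. Section 8 defines the observation period as running to 3 months after surgery, with no exception for discontinued patients. This stands in part: the end of data collection is inferred, and a reader should not take it as stated. But after a single dose there is nothing else for 9-2 to end, and no section says that follow-up continues.

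Serious events are also not simply lost. Reporting under section 10-2 is triggered when the investigator recognises the event and does not depend on continued participation. That is true, but it covers only events judged possibly related to drug or procedure, and it does not replace the 14-day and 3-month assessments. Section 16-3 promises care for adverse reactions after discontinuation, not outcome collection.

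Knowledge of allocation is limited to patients whose key was opened; otherwise the physician is blinded. That also stands. Knowledge of the outcome needs no key opening.

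Three stronger readings are tempting but not supported:
- **Both criteria damage the non-inferiority and mRS analyses alike.** mITT probably removes the criterion 2 patients anyway.
- **A patient made too unstable to scan by a complication could be dropped under the MRI exclusion.** Exclusion 8 is an entry criterion, and nothing in the protocol extends it to later instability.
- **A few missed bleeds would reverse the safety conclusion.** With 242 per arm and 12 placebo bleeds, the Wald upper limit is 10.5 points at 26 aspirin bleeds and 9.6 at 24. This shows only that a result placed beside the margin is fragile. The counts are invented. Setting the 12-per-arm allowance against the margin would likewise assume that every lost patient had an event and that all losses fell in one arm.

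**Conclusion.** The point holds in a limited form. Section 9-2 contains two grounds, neither of them the patient's choice, on which a dosed patient can be discontinued when only observation is left to end, and the protocol does not require the later assessments to continue. Criterion 4 is the main concern: it reaches the mITT non-inferiority and mRS analyses, and the second primary outcome if applied before the MRI. Criterion 2 mainly affects the completeness of the safety and ITT sets.

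The bias cannot be sized from the protocol. The range of about 1 to 4 points against a 10-point margin rests on assumed loss in the aspirin arm only and on assumed bleeding rates. It shows that the effect could matter, not that it will. A reader might infer that the bleeding comparison is already invalid. The documents do not support that, since they do not show how often these criteria will be used.

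**What to change.** Amend section 9-2 to say that, once study drug has been given:
- criteria 2 and 4 do not end outcome collection;
- such patients continue to the scheduled outcome assessments: imaging where it can safely be done, 14-day events, and 3-month mRS, by telephone if needed as section 6 already allows;
- only withdrawal of consent to further data collection, or closure of the study, ends follow-up;
- ineligibility found late is recorded as a protocol deviation.

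Keep the section 9 requirement to record the reason and to examine the patient at discontinuation. Patients who withdraw consent after dosing still need it.

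The cost is a short amendment and follow-up of a few more patients. No clinical rule changes. The amendment helps only patients still under observation, because assessments already missed cannot be recovered.
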